**PURPOSE OF PROTOCOL:**

1. To compare the inflammatory responses (primarily PKC activation in monocytes), between Far-East Asian Americans and Caucasian Americans, when they change from a traditional Asian diet to a typical American diet.
2. To correlate the biochemical changes of inflammatory responses in the plasma and monocytes with those in the gingival crevicular fluid (GCF).

**STUDY DESIGN:**

This is an 18-week (2 weeks run-in and 16 weeks diet intervention), randomized controlled study involving 50 non-diabetic subjects with family history of diabetes. Subjects can be normal glycemic, have family history of impaired fasting glucose, gestational diabetes or have impaired glucose tolerance but cannot have frank diabetes, defined by the American Diabetes Association Clinical Guidelines*[[1]](#endnote-2)*. Family history of diabetes is defined as subjects having a first degree relative and grandparents diagnosed with diabetes mellitus. One half of the subjects (n = 35) will be Asian Americans of Far-East Asian decent (Korean, Japanese, Chinese) while the other half (n = 35) will be Caucasian-Americans. All subjects will follow 8 weeks of Asian diets (Visit 2) after 2 weeks of run-in period. At Visit 3, subjects will be randomized. 10 out of the 35 subjects in the Asian group and 10 out of the 35 subjects in the Caucasian group will be randomized to continue following Asian Diet (AD) for another 8 weeks, serving as controls. The remaining 25 individuals, in both the Asian and Caucasian cohorts, will be randomized to switching to 8 weeks of Western Diet (WD). Eight weeks of controlled diet has been shown in previous studies to be adequate in detecting differences in blood lipids and blood pressure.*[[2]](#endnote-3)*

| **Asian (n = 25)** | | **Caucasian (n = 25)** | |
| --- | --- | --- | --- |
| **Intervention Diet**  **(N = 20)** | **Control Diet**  **(N = 5)** | **Intervention Diet**  **(N = 20)** | **Control Diet**  **(N = 5)** |
| AD for 8 weeks | AD  (16 weeks) | AD 8 weeks | AD  (16 weeks) |
| WD for 8 weeks | WD 8 weeks |

**AD** = Asian Diet; **WD** = American (Western) Diet

**Table 1** is a graphical presentation of study design.

The dietary composition of this study was designed to reflect the proportion of the various macronutrients in traditional Asian and Westernized diets although the actual foods or combination of foods are not necessarily the same as those found in traditional rural Asian (AD) or typical Western diets (WD).

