###### DATA ANALYSIS / SUBJECT SELECTION

**Statistical Considerations**:

**Sample size and power calculations**:

This study is a pilot/ feasibility study. The primary hypothesis of this study is to compare changes in PKC activity due to the transition from a traditional Asian diet to a typical American diet in two different ethnic groups, Asian and Caucasian. The interest is the mean percent change in marker levels between the two ethnic groups, which would be the values at timepoint 3 (after exposure to American diet) minus the values at timepoint 2, divided by the measure at time point 2 times 100. This would give the percent change that could be accounted for by exposure to the different diets in each ethnic group. For this comparison, the power for comparing the net change between the two ethnic groups of 20 individuals who will change from a traditional Asian diet to an American diet was calculated. Additionally, two control groups (one of each ethnicity) will remain on the traditional Asian diet as a control for potential outside effects on the primary hypothesis, the power calculations for comparing the control group to the active group can also be found below.

A total of 25 individuals of each ethnic group will be randomized into either the traditional Asian diet group (n=5) for each period or into the traditional diet and then the American diet (n = 20). The total number of participants is limited by cost. It is our hope that the 5-person control arms makes it possible to assess whether a factor outside of diet contributed to any differences observed. These control groups of ten will only be used for a subset analysis to get an idea of possible environmental effects on the outcome of interest, change in PKC activity. An appropriate two-sample test will be used for this determination, with the alpha and power given in the proceeding paragraph.

The power for the examination of percent change in PKC activity, the primary hypothesis, was calculated using STATA 7.0 (College Station, Texas 2001). An assumption of a one-sided test with an alpha of 0.05 was made. Mean PKC measurements were estimated at 78.1*[[6]](#endnote-7)* ±5 (there is no expected ethnic variation in PKC activity levels). Calculations are based on change exhibited by cardiac cells with exposure to increased lipids. In previous trials a 50% change has been observed in PKC activity in the cytosol of cardiac cells.

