Table 1. Power calculations for PKC activity percent change to detect a difference between Caucasian and Asian American groups when exposed to the American diet.

| **Size of Group 1** | **Size of Group 2** | **Percent change** | **PKC estimate** | **PKC Std dev (+)** | **Power** |
| --- | --- | --- | --- | --- | --- |
| 25 | 25 | 10 | 85.91 | 5.5 | 0.999 |
| 25 | 25 | 5 | 82.005 | 5.25 | 0.8527 |

This summary table of power to detect a significant difference suggests that a study using this approach would have adequate power to detect a difference between the two groups in PKC activity. We do not expect to see a difference less than 5%.

Table 2.  Power calculations for PKC activity change with change in diet based on a comparison to detect a difference between the control group and those exposed to the American diet. The baseline PKC activity value used in this calculation is 78.1 5.

| **Size of Group 1** | **Size of Group 2** | **Percent change** | **Comparison values** | **Power** |
| --- | --- | --- | --- | --- |
| 10 | 25 | 10 | 85.91 5.5 | 0.969 |
| 10 | 25 | 5 | 82.005 5.25 | 0.875 |

This demonstrates that we have adequate power to detect as low as a 5% change between the two groups. This exceeds our needs as estimated change is approximately 50%.

In addition to the primary endpoint of change in PKC levels, changes in Flow Mediated Dilation (FMD) and CRP are of interest. These differences will be examined by two-sample tests, either two-sample t or Wilcoxon sign rank. The power curves based on current literature for changes in FMD can be found below, based on a one-sided hypothesis using an alpha of 0.05, for the detectable difference of percent change between ethnic groups. The power to detect a difference in percent change for CRP measures was also examined. Our estimates indicate that there is insufficient power (~50%) to detect a difference as large as 25 between the two percent change measures. This was calculated assuming a one-sided test with an alpha of 0.05.

 Additionally, we present the power curve for the detection of difference in percent change in Flow Mediated Dilation.

Figure 1. Power curve for percent difference in FMD between Caucasians and Asians (the x-axis represents difference between the two measures) [[7]](#endnote-8),[[8]](#endnote-9) ,[[9]](#endnote-10),[[10]](#endnote-11)

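### The protocol describes two trial sizes, 50 subjects (20 + 5 per ethnicity) and 70 (25 + 10); both power tables use the larger one although the text says groups of 20

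*Protocol*

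**What the plan says.** Two sizes stand side by side in the protocol.

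- **50 subjects.** The Study Design section opens with a "randomized controlled study involving 50 non-diabetic subjects with family history of diabetes". Its design table is headed "Asian (n = 25) | | Caucasian (n = 25", with 20 on the intervention diet and 5 on the control diet in each ethnicity. The Periodontal Diagnosis section also counts fifty participants. The sample-size section agrees: "A total of 25 individuals of each ethnic group will be randomized into either the traditional Asian diet group (n=5) for each period", with 20 per ethnicity switching diet.
- **70 subjects.** Between the opening sentence and the design table, the Study Design prose says "One half of the subjects (n = 35) will be Asian Americans of Far-East Asian decent" and gives the same number for Caucasians. It goes on: "10 out of the 35 subjects in the Asian group and 10 out of the 35 subjects in the Caucasian group will be randomized to" stay on the Asian diet, and "The remaining 25 individuals, in both the Asian and Caucasian cohorts, will be randomized to switching to 8 weeks of Western Diet (WD").

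On power, the sample-size section says that what was calculated is "the power for comparing the net change between the two ethnic groups of 20 individuals" who switch diet. The 5% row of power Table 1 nevertheless reads "25 | 25 | 5 | 82.005 | 5.25 | 0.8527", that is, 25 per group. Power Table 2 (control against switchers) uses 10 against 25. The sample-size text speaks of five-person control arms and, in the next sentence, puts the control groups at ten.

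**The concern.** Half of 50 is not 35, and nothing in the protocol says which version is current. Three things depend on the answer.

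- **Enrolment.** The totals differ by 20 subjects, 40% of the smaller one, in a study whose size is said to be limited by cost.
- **Allocation.** The envelopes opened at Visit 3 must be prepared in advance, at either 5:20 (5/25 = 20% control) or 10:25 (10/35 = 29% control) within each ethnicity. Both cannot be followed.
- **Stated power.** If 50 subjects are enrolled, both power tables describe groups that will not exist.

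**Working it through.** **Inputs** (sample-size section and power Tables 1 and 2): reference PKC mean 78.1, SD 5. Comparison mean 82.005, SD 5.25 (5% row) or 85.91, SD 5.5 (10% row). One-sided alpha 0.05, so z = 1.645.

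**Formula** (two-sample normal approximation, unequal SDs): power = Φ( difference / √(SD₁²/n₁ + SD₂²/n₂) − 1.645 ).

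**Power Table 1, 5% row as printed.** Difference = 82.005 − 78.1 = 3.905; SD₁² + SD₂² = 25 + 27.5625 = 52.5625.
- 25 v 25: √(52.5625/25) = 1.450; 3.905/1.450 = 2.693; 2.693 − 1.645 = 1.048; Φ = **0.8527**. This matches the printed figure to four decimals, so the table was computed with 25 per group.

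**The same row at the group size named in the text.**
- 20 v 20: √(52.5625/20) = 1.621; 3.905/1.621 = 2.409; 2.409 − 1.645 = 0.764; Φ = **0.7775**.
- Variants at 20 v 20: noncentral t 0.764; common SD of 5, 0.795; two-sided 0.673.

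**Power Table 1, 10% row.** Difference 7.81: 0.9998 at 25 v 25 (printed 0.999) and 0.9989 at 20 v 20. The smaller size hardly matters here.

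**Power Table 2, same formula, control group first.**

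| Sizes | 5% row | 10% row |
|---|---|---|
| Printed, 10 v 25 | 0.875 | 0.969 |
| Recomputed, 10 v 25 | 0.66 | 0.992 |
| 5 v 20 (50 subjects, within ethnicity) | 0.46 | 0.92 |
| 10 v 40 (50 subjects, ethnicities pooled) | 0.71 | 0.996 |

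For example, 10 v 25 at 5%: √(25/10 + 27.5625/25) = √3.6025 = 1.898; 3.905/1.898 = 2.057; 2.057 − 1.645 = 0.412; Φ = 0.66. The printed 0.875 is therefore not reproduced even at the table's own sizes.

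**How far 0.78 can be trusted.** The endpoint is percent change within subject, but Table 1 compares two cross-sectional means. The SD of percent change is not given. As an assumption, approximate it by 100·√(5² + 5.25² − 2ρ·5·5.25)/78.1, with within-subject correlation ρ. For a 5-point difference, one-sided:

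| Assumed ρ | SD of percent change | Power, 20 per group | Power, 25 per group |
|---|---|---|---|
| 0 | 9.28 | 0.52 | 0.60 |
| 0.5 | 6.57 | 0.78 | 0.85 |
| 0.8 | 4.16 | 0.98 | 0.995 |

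**The case against.** **The 25 in power Table 1 could be the whole ethnic cohort (20 + 5) of the 50-subject design.** This does not hold. The table is headed as a comparison of groups exposed to the American diet, and the five controls never receive it. The text names groups of 20. The 10 v 25 of Table 2 fits no control-against-switcher split of 50 subjects, which would be 5 v 20 within ethnicity or 10 v 40 pooled.

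**The loss of power is small and the study is a pilot.** This largely stands. One row falls by 7.5 points and the other is barely touched. The protocol calls itself a pilot/feasibility study and cites a change of about 50%, although that figure concerns change with diet, not the difference between ethnic groups.

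**A reader might infer that the primary analysis has 78% power and misses a required 80%.** The documents support neither part. The 0.78 inherits Table 1's cross-sectional SDs, and the power for percent change is unknown without its SD. The protocol claims only adequate power and names no 80% threshold. Its remark about differences under 5% is an expectation, not a declared minimum difference of interest.

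**A reader might also infer that 50 is the intended size, and that the control groups of ten are two fives pooled.** More places agree with 50, but no text says that it governs. The ten could equally be left over from the 70-subject version.

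**Conclusion.** The contradiction is real and lies in the current text: 50 subjects at 20 + 5 per ethnicity against 70 at 25 + 10. It has to be resolved because enrolment and the randomisation envelopes depend on it.

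Both power tables carry the 70-subject arm sizes, contrary to the text that introduces them. On Table 1's own inputs and one-sided 0.05, the stated 0.8527 at a 5% difference belongs to 25 v 25; at 20 v 20 it is about 0.78, and the 10% row remains about 0.999. Table 2's 5% figure of 0.875 is not supported under either size: about 0.66 at 10 v 25, 0.46 at 5 v 20, and 0.71 at 10 v 40.

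All these figures rest on the protocol's simplification of comparing two cross-sectional means. They show that the printed tables do not fit the stated design; they do not establish the true power for percent change.

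**What to change.** The sponsor should state one enrolment total and one allocation split, and use them in the Study Design prose and table, the Periodontal Diagnosis section, the sample-size text and both power tables. The sentence that puts the control groups at ten must be made to match the chosen split.

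- **If 50 is kept:** change the Study Design prose to 25 per ethnicity, 5 controls and 20 switchers. Recompute power Table 1 at 20 v 20 (5% row about 0.78, 10% row about 0.999). Recompute power Table 2 at 5 v 20 (about 0.46 and 0.92), or at 10 v 40 if controls are to be pooled across ethnicities (about 0.71 and 0.996), and say which.
- **If 70 is kept:** correct the opening 50, the design table, the fifty in Periodontal Diagnosis, and the 25, 20 and 5 in the sample-size section. Recompute power Table 2 at 10 v 25 (5% row about 0.66 instead of 0.875; 10% row about 0.992 instead of 0.969).

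In either case, say beside the tables that they rest on cross-sectional SDs and that the SD of percent change is not known.

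The cost is wording and two recomputed tables, with less favourable stated power at the 5% difference. Keeping 50 needs no extra subjects; keeping 70 means 20 more than the opening sentence states.

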**Asian Diet (AD)**

- About 70% carbs, 15% protein, 15% fat (20% sat fat) less than 1% trans fats, 15g

fiber/1000kcal

- Caloric distribution: 25% breakfast, 40% lunch, 25% dinner, 10% after dinner/bedtime snacks
- For details, please see study summary flow sheet

**Western/ American Diet (WD)**

- About 50% carbs, 16% protein, 34% fat (20% sat fat), 4% trans fats, 6g fiber/1000kcal
- Caloric distribution: 25% breakfast, 40% lunch, 25% dinner, 10% after dinner/bedtime snacks
- For details, please see study summary flow sheet

Veronique Corporation will prepare and package all the diets for the study. Raw ingredients and commercially prepared food products will be provided by Veronique Corporation and Sunstar Inc. in Japan. The research dietician will work with a chef with a specialty in Japanese, Korean and Chinese cuisines to increase palatability of meals served. To ensure quality of the meals, Tokyo City, Yang’s Inc. will prepare and deliver a test meal once a month for food tasting by research staff members. Study investigators will also visit the facility to inspect the operations and document the findings on a monthly basis.

Subjects will be instructed to consume only the 3 meals and one snack a day provided except for non-sugar containing beverages. A list of snacks allowed will be provided. Subjects’ dietary habits will also be assessed by 24-hr dietary recall. If they consume alcoholic or caffeinated beverages, they will be advised to maintain their usual intake record consumption of these beverages during the study. Subjects will be provided instructions about compliance at the beginning of the study and reinforced throughout the study. They will be asked to maintain their weight and keep their physical activities constant throughout the study. Complete consumption of food provided is highly encouraged and any leftovers will be recorded. Subjects will estimate the percentage of each food item that is not consumed and record this information on a weigh-back form. A dietitian will briefly meet with each subject bi-weekly to measure weight, adjust caloric intake as necessary, ensure compliance, and answer any questions subjects may have. Caloric intake of +/- 250 kcals will be adjusted bi-weekly for subjects with weight change of more than +/- 2 kg from the baseline weight.

Subjects will be scheduled to 4 main visits: **Visit 1** - Screening, **Visit 2** – Asian Diet phase, **Visit 3** – AD or WD phase, and **Visit 4** – final visit. At these visits, anthropometric measurement, lab assessments and DEXA scan will be performed. All subjects will undergo a dental screening questionnaire at the beginning of the study to assess gum health. Subjects will also be scheduled to 6 additional visits to Joslin for weight measurement. All subjects will undergo periodontal evaluation and gingival crevicular fluid (GCF) extraction at each visit at Harvard School of Dental Medicine and Doppler forearm Sonography will be performed at Joslin Diabetes Center.

##### Details of Subjects

A thorough search of the patient database (IDX and NextGen) at the Joslin Clinic and the Asian Clinic at Joslin will be undertaken to identify subjects with history of diabetes who have not, according to Joslin records, voluntarily opted out to be contacted for potential research studies. Since we are not studying diabetic individuals but individuals with family history of diabetes and medical history of IGT, IFG and GDM, we will contact these individuals to ask their family members who may be interested to contact us for screening. In addition, we will enlist eligible Far East Asian Americans from: local Asian community health centers, from various college campuses and Asian American organizations. This will be done through advertisements placed on bulletin boards at medical centers, schools, or through referrals from colleagues. Subjects will also be recruited from fliers, advertisements, or through posting on the Internet. Invitation letters will be sent to eligible subjects. Advertisement samples will be presented for IRB approval prior to use. Subjects will receive informed consent form via mail prior to the initial visit. During the initial contact, a study investigator will explain the purpose, nature, and potential risks of the study in detail to the potential volunteer in languages they can understand. We plan to only include subjects who can understand English. If other Asian languages are needed to facilitate communication with subjects, they will be developed by professional translators and submitted for IRB approval. Brief questions will be asked to confirm demographic and medical information for eligibility. They will be given time to ask questions and make appointment for screening.

**Details of Study Procedure(s)**

**Visit 1 – Screening (Week 0 – Week 2)**

Prior to Visit #1, all subjects will be screened by a checklist (base on inclusion/exclusion criteria listed in Part C). Each will be asked to fast before coming to the visit.

Eligible subjects will be scheduled for **Visit 1 (beginning of week 0)** with a study physician who will collect the consent forms from Joslin Diabetes Center and Beth Israel Deaconess Medical Center. Medical history, physical examination, anthropometric measurements, blood tests, blood pressure, pregnancy tests for females, and an oral glucose tolerance test will be performed after this. Those who have blood glucose results > 200mg/dl from oral glucose tolerance test will be excluded from the study. A registered dietician will perform a 24-hour diet recall, counsel the dietary procedures and use of accelerometer. Total Energy Expenditure (TEE) for each subject will be calculated to determine caloric intake using the following equation:

**Mifflin-St.Jeor equation:*[[3]](#endnote-4)***

**Men:** (10 x w) + (6.25 x h) - (5 x a) + 5

**Women:** (10 x w) + (6.25 x h) - (5 x a) - 161

W = weight (kg) h = height (cm) a = age

**Activity Factors:**

An activity factor of 1.35 will be used with Mifflin-St.Jeor equation to determine subjects’ initial total energy expenditure. This activity factor has been documented to be applicable for weight maintenance in healthy non-overweight adults.*[[4]](#endnote-5)* We will ensure weight stability by adjusting +/- 250 kcals each week for a weight change of +/- 2 kg from baseline weight per week.

Since subjects are encouraged to maintain weight, a self-administered questionnaire will be used to monitor their activity levels throughout the study.*[[5]](#endnote-6)* In addition, we will also use the Actiped to monitor physical activity levels of all subjects. This questionnaire will be given at Visit 2, 3 and 4.

All subjects will receive a dental examination and a full mouth dental x-ray at the HSDM. HSDM investigators will explain dental procedures in detail. Subjects will then be asked to sign the HSDM ICF. They will also complete questionnaire about general health and quality of life.

During these 2 weeks of screening period, subjects are required to maintain their usual weight and physical activities.

**Visit 2 - AD (Week 2 – Week 10)**

Subjects will be required to fast before this visit. Urine for albumin, blood tests, weight, anthropometric measurements, vital signs and DEXA scan will be performed. Subjects will be assessed for arterial endothelial function by forearm Doppler Sonography at Joslin Diabetes Center and baseline dental evaluation for periodontal diseases will be performed at the Harvard School of Dental Medicine (HSDM). (For specific dental procedures, please see “Dental Procedures” below).

The study dietician will provide instructions to all subjects on beginning 8 weeks of **Asian Diet (AD)** prepared by Veronique Corporation. Subjects are required to only consume food (3 meals and a snack/day) provided for the rest of the study (except for non-sugar, non-alcohol containing beverages, a list will be provided) and continue to keep food weigh-back sheets. Foods throughout the entire study will be prepared and packaged by Veronique Corporation. Complete consumption of food provided is highly encouraged and any leftovers will be recorded. Subjects will estimate the percentage of each food item that is not consumed and record this information on a weigh-back form. A dietitian will briefly meet with each subject bi-weekly to measure weight, adjust caloric intake as necessary, ensure compliance, and answer any questions subjects may have. Caloric intake of +/- 250 kcals will be adjusted bi-weekly for subjects with weight change of more than +/- 2 kg from the baseline weight.

**Visit 3 - WD or AD (Week 11 – 18)**

At Visit 3 (End of Week 10), all subjects will receive an envelope that will determine if subjects will be randomized to the control (continue another 8 weeks of Asian Diets) or the intervention group (switching to 8 weeks of Western Diets). Anthropometric measurement, DEXA scan, weight, OGTT, vital signs, and blood tests including inflammatory markers will be repeated. Requirements in this phase will be the same as Visit 2. Subjects will be asked to complete a questionnaire about General health and quality of life. All subjects will also complete a Diet Palatability Survey, receive a forearm ultrasound evaluation at Joslin Diabetes Center and dental examination at HSDM. All subjects will fast before coming to this visit. While the **Control group(a)** will continue on AD, the **Intervention group(b)** will switch from AD to 8 weeks of WD prepared and packed by Veronique Corporation. starting from this visit.

